The secondary endpoints are as follows:N75-P100 amplitude decline rate compared to baseline measured under TIVA, calculated by the formula $$\frac{\left[N75-P100\left(TIVA\right)-N75-P100\left(HD\right)\right]}{\left[N75-P100\left(TIVA\right)\right]}\times100\%$$ or $$\frac{\left[N75-P100\left(TIVA\right)-N75-P100\left(LD\right)\right]}{\left[N75-P100\left(TIVA\right)\right]}\times100\%$$. N75-P100 (TIVA) will be measured 30 min after anesthesia induction under TIVA in both groups. N75-P100 (HD) or N75-P100 (LD) will be measured 60 min after anesthesia induction in HD or LD group.P100-N145 amplitude decline rate compared to baseline measured under TIVA, calculated by the formula $$\frac{\left[P100-N145\left(TIVA\right)-P100-N145\left(HD\right)\right]}{\left[P100-N145\left(TIVA\right)\right]}\times100\%$$ or $$\frac{\left[P100-N145\left(TIVA\right)-P100-N145\left(LD\right)\right]}{\left[P100-N145\left(TIVA\right)\right]}\times100\%$$. P100-N145 (TIVA) will be measured 30 min after anesthesia induction under TIVA in both groups. P100-N145 (HD) or P100-N145 (LD) will be measured 60 min after anesthesia induction in HD or LD group.Rate of prolongation of P100 latency compared to TIVA baseline measurements, calculated by the formula $$\frac{\left[P100\left(HD\right)-P100\left(TIVA\right)\right]}{\left[P100\left(TIVA\right)\right]}\times100\%$$ or $$\frac{\left[P100\left(LD\right)-P100\left(TIVA\right)\right]}{\left[P100\left(TIVA\right)\right]}\times100\%$$. P100 (TIVA) will be measured 30 min after anesthesia induction under TIVA in both groups. P100 (HD) or P100 (LD) will be measured 60 min after anesthesia induction in HD or LD group.The success rate of FVEP monitoring is defined as the ratio of the number of eyes with a satisfactory waveform to the number of all monitored eyes.FVEP stacking satisfaction will be assessed by electrophysiologists. A satisfactory waveform that could be evoked no more than three times will be considered satisfactory.Intraoperative anesthetic and vasoactive drug dosage, including anesthetics (i.e., sufentanil, remifentanil, propofol, rocuronium) and vasoactive agents (i.e., atropine, ephedrine, noradrenaline, phenylephrine, urapidil)Recovery quality:Respiratory recovery time is defined as the time from the cessation of anesthesia to the patient’s spontaneous breathing.Eye-opening time is the time from anesthesia cessation to when the patient can be called to open their eyes.Extubation time is defined as the time from the cessation of anesthesia to the removal of the patient’s tracheal catheter.Post-extubation agitation score. Ratings will be performed immediately after awakening and 15, 30, and 60 min after awakening: 1 point—restful sleep; 2 points—awake and calm; 3 points—irritability or irritability or crying; 4 points—difficulty to comfort or uncontrollable crying; 5 points—unable to be quiet or confused or delirium.Post-extubation sedation score. Ramsay sedation scale will be administered to the patients immediately after awakening and at 15, 30, and 60 min after awakening: 1 point—awake but anxious and restless; 2 points—cooperation, orientation, quiet; 3 points—drowsiness and response to commands; 4 points—drowsiness, rapid response to tapping eyebrow or loud auditory stimuli; 5 points—lethargy, slow response to tapping eyebrow or loud auditory stimuli; 6 points—drowsiness, no response at all. Scores 2–4 indicate satisfactory sedation and 5 to 6 excessive sedation.

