### Statistical analysis

All data analyses will be performed on both a per-protocol (PP) and intention-to-treat (ITT) basis. The intent-to-treat population will include all subjects randomized to receive HD or LD anesthesia maintenance, and the completed FVEP data will be collected. The per-protocol population will include all subjects in the ITT population not identified as protocol violators (i.e., change in the anesthesia strategy after the trial initiates). These protocol violations will be shown in a listing. Subjects who do not obtain available FVEP data or abandon the study for various reasons will be considered to have failed HD/LD and will be excluded from any form of analysis. For the missing data, the last observation and the worst-case imputation scenarios will be used as the main interpolation method.

The statistical analysis will be performed by an independent statistician using SPSS V.25.0 (Somers, NY, USA). Histograms and the Shapiro‒Wilk test will be used to assess the normality of the data distribution. For the statistical description, the continuous variables will be presented as the mean (standard deviation, SD) for normally distributed data or median (interquartile range, IQR) for skewed distributions. Categorical variables will be reported as counts and percentages, and the relative risk with its 95% confidence interval (CI) will be calculated. The absolute standard deviation (ASD) will be determined to identify any imbalance in baseline characteristics.

The primary outcome (N75-P100 amplitude of FVEPs recorded 1 h after induction) will be analyzed using a superiority test. According to the results of other studies, the superiority margin was defined as 20% of the N75-P100 amplitude in the HD group [6].For secondary outcomes, *χ*^2^ tests or Fisher’s exact tests will be performed for categorical variables including N75-P100 amplitude decline rate, P100-N145 amplitude decline rate, rate of prolongation of P100 latency, success rate of FVEP monitoring, FVEP stacking satisfaction, adverse events related to FVEP monitoring, and recovery quality. Anaesthetic and vasoactive drug agent consumption will be analyzed using independent samples *t*-tests for normally distributed variables and Wilcoxon sum tests for variables with skewed distributions. The study will terminate after all the data for the last patient are collected.

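### Three percentage-change endpoints and three recovery times are continuous by definition, yet are listed as categorical and assigned chi-square or Fisher tests with no cut-off

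*Protocol article*

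**What the plan says.** The Study endpoints section of the protocol article sets the scale of each secondary outcome.

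- Three are percentage changes with an explicit formula: "N75-P100 amplitude decline rate compared to baseline measured under TIVA, calculated by the formula"; "P100-N145 amplitude decline rate compared to baseline measured under TIVA, calculated by the formula"; and "Rate of prolongation of P100 latency compared to TIVA baseline measurements, calculated by the formula". Each takes the change between the 30-minute TIVA value and the 60-minute value, divides it by the TIVA value and multiplies by 100%.
- Recovery quality includes three elapsed times: "Respiratory recovery time is defined as the time from the cessation of anesthesia" to spontaneous breathing; "Eye-opening time is the time from anesthesia cessation to when the patient can be called to open their eyes"; and "Extubation time is defined as the time from the cessation of anesthesia" to removal of the tube. It also includes an agitation score and a Ramsay score, each rated at four time points.

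The Statistical analysis section names, for chi-square or Fisher's exact tests, "categorical variables including N75-P100 amplitude decline rate, P100-N145 amplitude decline rate, rate of prolongation of P100 latency". The list continues to the success rate and ends with "FVEP stacking satisfaction, adverse events related to FVEP monitoring, and recovery quality". The t-test and the Wilcoxon test are reserved for anesthetic and vasoactive drug consumption. The same section says that categorical variables are reported as counts, percentages and relative risks. Its closing paragraph lists the secondary comparisons again, at a two-sided 0.05 level, and adds no threshold.

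**The concern.** The test assigned to an endpoint has to match its scale. A formula that returns one percentage per patient gives a continuous measurement, even when it is called a rate; it is not the proportion of patients with an event. The same holds for minutes to extubation. A chi-square or Fisher test ignores the order and size of the values, so it can address these endpoints only after they have been grouped, and the article states no grouping.

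An analyst who follows the text literally obtains an empty result. One who does not must change the test or supply a cut-off, and the article gives no rule for either. This matters because the stated aim covers latency as well as amplitude, and P100 latency is compared between groups only through the prolongation endpoint. This is a wrong assignment in the text, not a detail left for an analysis plan to fill in.

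**Working it through.** The plan states no figure of its own on this point, so there is none to reproduce. The check sets scale against test and then works out what the stated test would return.

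**Step 1. Scale against test**

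| Endpoint | Scale (Study endpoints) | Test (Statistical analysis) | Cut-off given |
|---|---|---|---|
| N75-P100 decline | percentage change | chi-square/Fisher | none |
| P100-N145 decline | percentage change | chi-square/Fisher | none |
| P100 latency prolongation | percentage change | chi-square/Fisher | none |
| Respiratory recovery time | elapsed time | chi-square/Fisher, through recovery quality | none |
| Eye-opening time | elapsed time | chi-square/Fisher, through recovery quality | none |
| Extubation time | elapsed time | chi-square/Fisher, through recovery quality | none |

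The only candidate threshold is 20%. It appears in the Background as a warning value for an amplitude fall, and under Sample size calculation and Statistical analysis as the superiority margin for the primary outcome. It is not attached to any secondary endpoint.

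**Step 2. Pearson's test on the uncategorised values**

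Input: 70 patients, 35 per arm (Sample size calculation). Assumption: all 70 values differ. This is realistic for the evoked-potential endpoints, because each value is an average of three measurements (Intervention section) before the ratio is taken.

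- The table has 2 rows and 70 columns, and each column total is 1.
- Expected count in every cell: 1 × 35/70 = 0.5.
- Contribution of each column: (1 − 0.5)²/0.5 + (0 − 0.5)²/0.5 = 0.5 + 0.5 = 1.
- Statistic: 70 × 1 = 70, on (2 − 1)(70 − 1) = 69 degrees of freedom, p = 0.44.

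The values themselves do not enter this calculation. The result is the same for identical arms and for arms that do not overlap at all.

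**Step 3. Fisher's exact test on the same table**

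With the margins fixed, every possible table has the same probability, 1/C(70, 35). No table is less probable than the observed one, so p = 1 in every case.

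**Step 4. If the values were split in two (illustration only)**

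The plan proposes no split. To show what one could cost, assume a normal outcome, a standardised difference d, a split at the median and 35 per arm. The proportions above the median are then Φ(d/2) and 1 − Φ(d/2). The t-test power uses the noncentral t distribution with 68 degrees of freedom and noncentrality d√(35/2). Both tests are two-sided at 0.05.

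| Assumed d | t-test power | Chi-square power after median split |
|---|---|---|
| 0.5 | 0.54 | 0.38 |
| 0.68 | 0.80 | 0.61 |
| 0.8 | 0.91 | 0.75 |

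**The case against.** The strongest defence is that a responder analysis was meant. The Background cites a 20% fall from baseline as a warning value, which is on the same scale as the amplitude-decline formulas, and relative risks are planned for categorical variables. The full protocol or an analysis plan may hold a cut-off. That reading is plausible for the two amplitude endpoints but is not stated, and it offers nothing for latency or the three times. It does limit the point: a reader might infer that the test can be run only with a cut-off chosen after seeing the data, and the documents do not support this, because a cut-off could still be fixed beforehand.

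Four other limits stand.

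- The recovery times are not named in the test list. They enter through the umbrella term, so their misassignment is less explicit than that of the three percentages.
- A reader might infer that the agitation and Ramsay scores are equally misassigned. They are not. A chi-square test on an ordered score at one time point is valid though inefficient, and the article itself groups Ramsay scores into satisfactory and excessive sedation.
- A reader might infer that the percentage changes are the main support for the primary claim. The article does not say so. The primary outcome is tested on its own against its margin, and the Discussion ranks latency below amplitude.
- A median split of a normal variable keeps 2/π = 0.637 of the information, so a reader might infer a loss of about 70 × (1 − 0.637) = 25 patients. No median split is planned and normality of these percentages is not claimed, so this is not a consequence of the plan.

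**Conclusion.** The point holds for six secondary endpoints: two amplitude declines, one latency prolongation and three recovery times. As written, their scale and their test contradict each other. On uncategorised values the Pearson test returns 70 on 69 degrees of freedom (p about 0.44) and Fisher's test returns 1, whatever the treatment does. The exact figures assume 70 analysed patients with no tied values. Times recorded in whole minutes may tie, and the figures would then change, but the test would still ignore their order and size. The planned categorical summaries are unsuitable for the same reason.

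The primary outcome, its margin and the sample size are untouched. The chi-square/Fisher assignment remains suitable in type for success rate, stacking satisfaction and adverse events. The error is clear, confined to secondary analyses and cheap to correct.

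**What to change.** In the Statistical analysis section, remove the three percentage changes and the three recovery times from the categorical list. Place them under the t-test or Wilcoxon rule already written for drug consumption, and report mean or median differences with confidence intervals. If a binary endpoint is intended for any of them, define it in Study endpoints with its cut-off, before unblinded analysis. Keep chi-square/Fisher for outcomes that are truly categorical.

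Two improvements are optional and not needed to cure the error: a baseline-adjusted analysis of covariance of the 60-minute P100-N145 amplitude and P100 latency, and a rank or ordinal method for the agitation and Ramsay scores.

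The cost is one paragraph of wording. No data collection, sample size or primary analysis changes.

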A 1-sided *P* value of 0.025 will be considered statistically significant for the primary outcome. If the confidence interval for mean differences of N75-P100 amplitude between LD and HD groups lied above the lower limit of *δ* with *P* < 0.025, we defined LD group will be superior to HD group. While all *P* values will be 2-sided with a significant level of 0.05 for the comparisons of N75-P100 amplitude decline rate, P100-N145 amplitude decline rate, rate of prolongation of P100 latency, success rate of FVEP monitoring, FVEP stacking satisfaction, anaesthetic and vasoactive drug agent consumption, and adverse events related to FVEP monitoring or recovery quality between the group LD and HD.

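### Every secondary comparison is called significant at two-sided 0.05, with no order, adjustment, link to the primary result or exploratory label

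*Protocol article*

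**What the plan says.** The Statistical analysis section fixes two decision rules. For the single primary outcome, a one-sided P "value of 0.025 will be considered statistically significant for the primary outcome", and superiority of the LD group is tied to the confidence interval for the N75-P100 difference against the margin. For everything else, P "values will be 2-sided with a significant level of 0.05 for the comparisons of N75-P100 amplitude decline rate, P100-N145 amplitude decline rate"; the list continues with "rate of prolongation of P100 latency, success rate of FVEP monitoring, FVEP stacking satisfaction", drug consumption, adverse events and recovery quality. That makes eight named families.

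The Study endpoints section breaks some of these families down. Drug use is itemised, "including anesthetics (i.e., sufentanil, remifentanil, propofol, rocuronium) and vasoactive agents (i.e., atropine, ephedrine, noradrenaline, phenylephrine, urapidil"). Recovery quality comprises three times (for example "Respiratory recovery time is defined as the time from the cessation of anesthesia" and "Eye-opening time is the time from anesthesia cessation", plus extubation time) and two scores. For the agitation score, "Ratings will be performed immediately after awakening and 15, 30, and 60 min after awakening"; the Ramsay score follows the same four times. The Follow-up section names two adverse events, intraoperative awareness and local infection.

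The article names no key secondary outcome, testing order, adjustment or familywise level, and does not describe the secondary outcomes as exploratory or supportive. It also says that all analyses are run on both the per-protocol and the intention-to-treat sets.

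**The concern.** A significance threshold applied to each of many comparisons, with no control over the set, lets chance produce results that the plan itself calls significant. This is a rule the article states, so it differs from a detail merely left to an analysis plan that is not shown.

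Two features of this trial make it matter. First, the primary test must clear a margin of 20% of the HD amplitude (0.20 × 2.37 = 0.474 μV on the pilot mean), whereas no margin is stated for the N75-P100 decline rate. The primary could therefore fail while a measure of the same waveform is declared significant, and nothing in the text limits how that is reported. Second, recovery quality is cited in the Background and Discussion as a reason for using desflurane, and recovery items make up 11 of the 27 listed comparisons (3 times + 4 agitation ratings + 4 sedation ratings).

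**Working it through.** The article gives no familywise error rate, so there is no figure of its own to reproduce. The only stated input is the level of 0.05, two-sided, per comparison.

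**Number of comparisons**

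- By family, as named in Statistical analysis: N75-P100 decline, P100-N145 decline, P100 latency prolongation, monitoring success, stacking satisfaction, drug consumption, adverse events, recovery quality = 8.
- By item and time point, from Study endpoints and Follow-up: 5 FVEP outcomes + 9 drugs (4 anaesthetics, 5 vasoactive agents) + 3 recovery times + 4 agitation ratings + 4 sedation ratings + 2 adverse events = 27.

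The article does not say how many tests will be run, so 8 and 27 are two readings of its lists. Repeating each test on both analysis sets adds further, highly correlated looks that neither count includes.

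**Independent true nulls**

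P(at least one P < 0.05) = 1 − 0.95^k, and expected false positives = 0.05 × k.

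| Tests counted | k | At least one false positive |
|---|---|---|
| Eight named families | 8 | 1 − 0.95^8 = 33.7% |
| All items and time points | 27 | 1 − 0.95^27 = 75.0% (0.05 × 27 = 1.35 expected) |
| Without propofol, which differs by design | 26 | 73.6% |
| Also without the two adverse events | 24 | 70.8% |

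The adverse events are dropped in the last row because, at assumed event rates of 1% to 2% and 35 patients per arm, Fisher's exact test rejects with probability below 0.0001. The total passes 50% from k = 14.

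The 33.7% is not a floor. Without N75-P100 decline, seven families give 1 − 0.95^7 = 30.2%. Leaving out success rate and adverse events as well, five give 1 − 0.95^5 = 22.6%.

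**Correlated true nulls**

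The documents give no correlations, so the values below are assumptions. The results come from 200,000 simulated draws of normal test statistics.

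| One common correlation, 27 tests | 0.2 | 0.3 | 0.5 | 0.7 | 0.8 |
|---|---|---|---|---|---|
| At least one false positive | 69% | 63% | 48% | 33% | 25% |

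A second structure uses 22 tests (no propofol, success rate, satisfaction or adverse events), correlated only within a domain (FVEP, drugs, recovery times, each score):

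| Within-domain correlation | 0.3 | 0.5 | 0.7 | 0.8 |
|---|---|---|---|---|
| Drugs correlated too | 64% | 59% | 52% | 46% |
| Drugs independent | 66% | 64% | 60% | 58% |

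**For comparison**

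Bonferroni over 27 tests would use 0.05/27 = 0.00185 each and hold the familywise rate at or below 5% under any dependence.

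**The case against.** The strongest reply is that the trial's main claim is already protected. There is one primary test at one-sided 0.025, and the article uses the word superior only for that test. The expected conclusion in the Discussion concerns FVEP monitoring, and both arms receive desflurane. A nominal 0.05 for supportive secondary outcomes is common practice, and an analysis plan that is not shown may add an order or a label. All of this stands as a limit on the point: the primary test, its error rate and the superiority rule are sound in this respect. It does not remove the point, because the article sets a significance rule for the secondary outcomes and nowhere says that they are only supportive.

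A reader might go further and infer that at least one false significant result is more likely than not, taking 75% as the expected rate. The documents do not support that:

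- They state no number of tests, and separate tests for each drug and each rating are an assumption.
- Propofol use differs by design.
- N75-P100 decline re-expresses the primary outcome, for which the pilot means of 3.43 and 2.37 μV point to a real difference.
- Awareness and infection will rarely produce a rejection. The same holds for success rate, which was 100% in the group's previous study.
- Sufentanil does not appear in the Anaesthesia regimen section, so that comparison may be empty.
- The recovery times share a starting point and each score is repeated on the same patient within an hour, so strong correlation is plausible.

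Nor does the text support inferring that a secondary result could by itself establish superiority of an arm.

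**Conclusion.** The concern holds for the secondary outcomes only. As written, each secondary comparison can be declared significant at two-sided 0.05 whatever the primary shows. The chance of at least one false declaration is well above 5%: about 34% for the eight named families and up to about 75% for all 27 items, both assuming independent true nulls. Correlation lowers the upper figure, to 48% at a common value of 0.5 and 33% at 0.7, and some of the listed comparisons are not nulls or will hardly ever reject. Whether the chance exceeds one half cannot be settled from the documents. The point should be corrected, but it does not threaten the primary conclusion.

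**What to change.** In the Statistical analysis section, replace the significance rule for secondary outcomes with a statement along these lines: secondary outcomes are supportive or exploratory; each is reported with an estimate, 95% CI and unadjusted nominal P; and no claim of statistical significance or of advantage for an arm rests on them, particularly if the primary test fails.

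If the sponsor wants confirmatory secondary claims, it should name a short list in advance and test it only after the primary succeeds, with a familywise method such as Holm at overall two-sided 0.05. Which measures go on that list is the sponsor's choice.

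The change is wording only and needs no extra patients or data. The cost is that some drug-use and recovery results can no longer be called significant. If a confirmatory list is used, Holm also costs a little power on its members.

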## Discussion

This randomized, controlled, patient- and assessor-blinded, and superiority clinical trial aims to assess the superiority effect of low inhaled concentration of desflurane combined with propofolremifentanil-balanced anesthesia versus high inhaled concentration of desflurane combined with remifentanil anesthesia on intraoperative FVEP monitoring. During flash light stimulation, the latencies of FVEPs in healthy eyes and eyes with visual impairment are widely distributed and overlap considerably [24, 25]. Therefore, using amplitude as an assessment and predictor is more meaningful than latency change. Thus, the primary outcome in this study is the N75-P100 amplitude of the FVEPs 1 h after the induction of anesthesia.

Neuromonitoring is usually performed under TIVA, which is also true for FVEPs. However, TIVA may not be suitable for lengthy surgeries needing motor-evoked potential monitoring with strict restriction for muscle relaxant supplements, especially during long-term spine surgery or neurosurgery. Intravenous-inhalation combined anesthesia has the advantage of synergistically acting on GABA and NMDA receptors that reduce the dosage of anesthetics and weaken the suppression of FVEPs. However, its impact on intraoperative FVEP monitoring has not been conclusive, and to the best of our knowledge, there are only a few relevant studies. In 2017, the Uribe study first proposed that compared with TIVA, desflurane-propofol balanced anesthesia greatly reduces the amplitude of FVEPs and prolongs their latency [16]. However, this study has many limitations. First, a combination of drugs was used for the balanced anesthesia group, including dexmedetomidine, remifentanil, and propofol. The doses of each drug were not clear. The synergistic effect of the combination of multiple drugs may aggravate the effects on FVEPs. Second, the range of BIS values was not strictly limited. Third, the small sample size (*n* = 19) may produce false positive or negative results. In 2021, we conducted a noninferiority study, which showed that the effect of sevoflurane 0.5 MAC combined with propofol and remifentanil-balanced anesthesia on the P100-N145 amplitude was not inferior to that of the TIVA group [17]. In our previous study, two groups of patients were controlled within the same BIS range combined with ERG monitoring, and the success rate of FVEP monitoring was 100%. Thus, our conclusion suggests a new anesthesia approach of sevoflurane-propofol balanced anesthesia maintenance for FVEPs besides TIVA. Yet, the effect of inhalation at different concentrations on FVEPs remains unclear. Desflurane has the advantage of high anesthesia recovery quality [22]. We hypothesize that desflurane-propofol balanced anesthesia can benefit the monitoring of FVEPs during spinal surgery compared with desflurane alone.

Wiedemayer et al*.* observed unstable waveforms of FVEPs in which the P100 latency was prolonged by 8–16%, and the P100-N145 amplitude was reduced by 60–67% under TIVA [26, 27]. In the present study, patients in the control group will receive desflurane-remifentanil anesthesia instead of total intravenous anesthesia. Due to the unique pharmacological advantages of desflurane with a low blood-gas partition coefficient and high quality of anesthesia recovery, a desflurane-remifentanil anesthesia maintenance strategy has been increasingly used in neurosurgery anesthesia [21]. In addition, there is no clinical data on the effect of desflurane inhalation anesthesia on intraoperative FVEPs. Also, an appropriate anesthesia regimen for FVEPs to protect visual function during surgery is an ongoing topic of interest among researchers.

The present study has a rigorous neuromonitoring and anesthesia regimen. In addition to anesthetic drugs, intraoperative monitoring of FVEPs is affected by hypothermia, hypotension, deep anesthesia, monitoring equipment, preoperative vision, surgical position, and surgical operations, such as drilling and flipping skin flaps [28]. This trial will be subject to rigorous inclusion and exclusion criteria, and a standardized process will be set up. In order to avoid visual function bias, all patients will be examined by an ophthalmologist to ensure normal visual function 1 day before the surgery. We will adjust the plasma concentration of propofol in the LD group and titrate the MAC of desflurane between 0.7 and 1.0 to strictly maintain the BIS between 40 and 50, primarily focusing and avoiding burst suppression. FVEPs will be monitored during quiet moments without any surgical manipulation. An intraoperative thermal blanket will be used to maintain axillary temperature between 36 and 37°C. Moreover, if intraoperative blood pressure exceeds the range of ± 10% of basal blood pressure, the anaesthesiologist will use vasoactive drugs, such as dopamine and urapidil, to maintain hemodynamic stability. FVEP stimulation, data recording, and storage will be performed using the Medtronic NimEclipse neuromonitoring system by the same experienced neuroelectrophysiologist.

In summary, this randomized, controlled, superiority trial aims to evaluate the suitability of low concentration of desflurane combined with propofol-remifentanil-balanced anesthesia for monitoring FVEPs during spinal surgery. The expected result is that low inhaled concentration of desflurane combined with propofol-remifentanil-balanced anesthesia is superior to high inhaled concentration of desflurane combined with remifentanil anesthesia for intraoperative FVEP monitoring. This study is expected to provide high-quality evidence for the effect of desflurane on FVEPs, aiming to explore a new feasible anesthesia scheme for the clinical application of FVEPs and visual function protection.

